##### Study Settings and Participants

Eligibility screening and recruitment will be identical to procedures used for phase I. We will partner with the Centre of Excellence for Research in AIDS (CERiA) at the University of Malaya, Kuala Lumpur, Malaysia. Eligibility criteria will include the following: (1) age ≥18 years; (2) cis-gender men; (3) laboratory-confirmed HIV negative status; (4) no existing use of PrEP; (5) own a smartphone; and (6) ability to understand, read, and speak English. Participants will be discontinued from the study under any of these circumstances: (1) acquisition of HIV infection (will be referred to appropriate care); (2) participant voluntarily chooses to leave the study; and (3) the provider thinks the study is no longer in the best interest of the participant.

Participants will be recruited using both in-person and online recruitment strategies. For in-person recruitment, flyers will be given out to potential participants as well as posted at local community-based organizations. In addition, various general and MSM-specific social media and other online platforms will be chosen as venues for participant recruitment. These include placing advertisements in geosocial networking apps popular among MSM in Malaysia (eg, Grindr, Hornet) as well as posting study flyers on Malaysian MSM–focused Facebook pages. The recruitment materials will include brief information about the study and contact information (and a link to the study website) where potential participants could receive more information.

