##### Primary Outcomes

All structured interviews will be assessed online via Qualtrics (Qualtrics XM). Primary outcomes are those along the HIV prevention cascade, including uptake of HIV testing (ie, ordering of HIV self-testing kit and uploading the result via the app or HIV testing as part of the PrEP clinical care) and PrEP (ie, current use of PrEP; yes/no). Both HIV testing and PrEP uptake will be assessed at each follow-up time point (3, 6, and 9 months) using self-report and medical record review for confirmation.

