##### Secondary Outcomes

Secondary outcomes include adherence and persistence on PrEP (for those who initiated PrEP). PrEP adherence will be assessed using (1) dried blood spot testing at 3-, 6-, and 9-month follow-ups, which will quantify tenofovir-diphosphate and emtricitabine-triphosphate in red blood corpuscles [45-48]. Tenofovir-diphosphate ≥700 fmol/punch will be defined as optimal adherence; and (2) self-reported adherence, which will be measured using the validated Visual Analog Scale [49]. Persistence on PrEP will be measured based on the completion of quarterly PrEP visits (recorded on the app).

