	**PrEP^b^** **adherence^c^**											
		Dried blood spot testing					✓		✓		✓	
		Visual Analog Scale					✓		✓		✓	
		Online PrEP script^c,d^					✓		✓		✓	
	PrEP persistence^c^						✓		✓		✓	
Focus groups												✓
Payment						✓		✓		✓		✓

^a^Treatment as usual (restricted access to the JomPrEP app features).

^b^PrEP: pre-exposure prophylaxis.

^c^Only applies to those who initiated PrEP.

^d^Only applies to the JomPrEP group.

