##### Analytical Plan

To test the hypothesis that the intervention group (I=JomPrEP) will be significantly more effective than the TAU group for HIV testing and PrEP uptake, we will compare the proportion for both outcomes. The null hypothesis is that the proportion of HIV testing and PrEP uptake in the intervention group and TAU is equal, expressed as follows: H_0_: p_I_=p_TAU_, where p_I_ and p_TAU_ are the proportion of HIV testing and PrEP uptake in the JomPrEP and TAU groups, respectively. Our alternative hypothesis is H_1_: p_I_>p_TAU._ We will use both intent-to-treat (ITT) and on-treatment analyses, with ITT used for efficacy. Baseline characteristics will be tested for homogeneity across the 2 groups using a *t* test or Wilcoxon rank sum test for continuous variables and chi-square test or Fisher exact test for categorical variables. Any baseline variable showing a significant difference at *P*<.05 between the 2 groups will be put into the model for adjustment. For all outcome variables assessed over a 9-month follow-up period, plots of longitudinal data over time will be provided. Prior to the primary analysis, the distribution of the missing data pattern will be examined across the 2 groups. For a subgroup of those starting PrEP, we will compare PrEP adherence using the same method and PrEP persistence using time-to-discontinuation and Cox proportional hazards ratios.

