The framework for testing the study hypotheses will compare the differences between the 2 groups (JomPrEP vs TAU) over time. To test our primary hypotheses on binary outcomes of HIV testing and PrEP uptake, a generalized linear mixed model [50] with random subject effects will be built to account for the correlation in repeated measurements within participants. Treatment assignment, time, the interaction between time and treatment assignment, and any other hypothesized confounders will be included as covariates. HIV testing and PrEP uptake proportion at the 9-month follow-up will be estimated and compared using a linear contrast statement in SAS PROC GLIMMIX. Similar analyses will be conducted for the secondary binary outcomes: optimal adherence and PrEP persistence. As an alternative analytical plan for assessing the impact of the 2 groups on adherence to PrEP, continuous adherence variables will be analyzed using a linear mixed model [50] with the same set of covariates as the binary adherence outcome and percent changes in adherence between the different assessment points will be estimated and compared between the 2 arms using the linear contrast statement in SAS PROC MIXED. For the aforementioned model, the covariance structure will be selected based on the fit statistics (eg, Akaike information criterion and the Bayesian information criterion) [51]. Given the several strategies by which PrEP adherence will be measured, we will utilize Spearman correlation coefficients and scatterplots to assess the associations between the biomedical measure (dried blood spot) [45-48] and self-report measure (Visual Analog Scale) [49].

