##### Sample Size

We calculated the sample size based on the difference we expect in the primary outcome (ie, PrEP uptake) by month 9. A sample size of 121 per group achieves 90% power to detect a 10% increase in PrEP uptake for the JomPrEP group compared with the TAU group, assuming 50% PrEP uptake in the TAU group at the 1-sided .05 significance level. A sample of 268 participants will be enrolled and randomized to the JomPrEP and TAU groups to accommodate a 10% dropout. Assuming 60% of PrEP uptake in the JomPrEP group, this sample size provides 85% power in detecting a standardized effect size of 0.5 for the secondary outcomes of adherence and persistence.

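### Adherence and persistence are compared only among men who start PrEP, a group formed after randomization, so the arm difference is not a randomized effect and may be biased in either direction

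*Protocol article*

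**What the plan says.** The restriction to starters appears in three places in the protocol article.

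- Secondary Outcomes: "Secondary outcomes include adherence and persistence on PrEP (for those who initiated PrEP".
- Table 1, footnote c, attached to the adherence and persistence rows: "Only applies to those who initiated PrEP".
- Analytical Plan: "For a subgroup of those starting PrEP, we will compare PrEP adherence using the same method". The same sentence puts persistence in this subgroup too, analyzed as time to discontinuation with a Cox model.

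Starting PrEP is a post-randomization event. Study Settings and Participants requires "no existing use of PrEP" at entry. Uptake is itself a primary outcome: "Both HIV testing and PrEP uptake will be assessed at each follow-up time point (3, 6, and 9 months". Sample Size is built on a difference in uptake, "assuming 50% PrEP uptake in the TAU group at the 1-sided .05 significance level" and 60% under JomPrEP. It then claims 85% power for a standardized effect of 0.5 on adherence and persistence.

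The Analytical Plan assigns ITT to efficacy and says that optimal adherence and persistence will be analyzed like the primary outcomes, with hypothesized confounders as covariates. As an alternative for continuous adherence, "percent changes in adherence between the different assessment points will be estimated and compared between the 2 arms". No definition of adherence that covers all randomized participants is given, and Limitations does not mention the selection.

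**The concern.** Randomization makes the two arms comparable as randomized. It does not make those who later start PrEP in one arm comparable with those who later start in the other. If JomPrEP succeeds on its primary outcome, its starters include men who would not have started under TAU. Any difference between these men and the rest is then counted as an effect of the app on adherence or persistence. Covariate adjustment may reduce this but cannot restore randomization.

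At stake is the meaning of both secondary outcomes. A real adherence benefit could be hidden or reversed, or an apparent benefit could come from who started and not from what the app did. The plan tests and powers the difference as a treatment effect, and nothing in the article warns the reader otherwise.

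The alternative continuous analysis has a smaller problem. Adherence has no baseline value, so changes can be taken only between post-randomization visits, and a benefit already present at month 3 and held steady would not show.

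**Working it through.** **1. Which population does the plan's power figure use?** Inputs from Sample Size: 121 evaluable per arm, 268 enrolled (134 per arm), uptake 50% and 60%, effect 0.5 SD. Normal approximation, two-sided 0.05: power = Φ(0.5/√(1/n₁+1/n₂) − 1.96).

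- 60% of 121 in both arms (72.6 each): 0.5/0.166 = 3.01; power 85.4%.
- 50% and 60% of 134 (67 and 80.4): 0.5/0.165 = 3.02; power 85.6%.
- 50% and 60% of 121 (60.5 and 72.6): 0.5/0.174 = 2.87; power 81.9% (89.0% one-sided).
- All 121 per arm: 0.5/0.129 = 3.89; power about 97%.

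The stated 85% is recovered on starters and not on everyone, which confirms the restricted population.

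**2. Share of JomPrEP starters without a TAU counterpart.** Two assumptions are needed: the 50% v 60% is read as initiation, and nobody who would start under TAU fails to start under JomPrEP. Then 50% start in either arm, 10% start only under JomPrEP, and the extra share is 10/60 = 1/6.

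**3. Effect on the comparison.** Let A be optimal adherence under TAU in men who start in either arm, δ the true effect of JomPrEP in those men, and a the adherence of the extra starters.

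- Starters-only difference = [0.50(A+δ) + 0.10a]/0.60 − A = (5/6)δ + (a − A)/6.
- All-randomized difference, non-starters counted as no = 0.50(A+δ) + 0.10a − 0.50A = 0.50δ + 0.10a.

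A = 70% and the values of a below are assumptions; the documents give none.

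| δ | a | Starters only, JomPrEP v TAU | Difference | All randomized, JomPrEP v TAU | Difference |
|---|---|---|---|---|---|
| 0 | 20% | 61.7% v 70% | −8.3 | 37% v 35% | +2 |
| 0 | 40% | 65.0% v 70% | −5.0 | 39% v 35% | +4 |
| 0 | 50% | 66.7% v 70% | −3.3 | 40% v 35% | +5 |
| 0 | 70% | 70.0% v 70% | 0 | 42% v 35% | +7 |
| 0 | 90% | 73.3% v 70% | +3.3 | 44% v 35% | +9 |
| +5 | 30% | 67.5% v 70% | −2.5 | 40.5% v 35% | +5.5 |

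With a true benefit of 5 points, the starters-only difference turns negative when (A − a)/6 exceeds (5/6)×5, that is when a is below 70 − 25 = 45%. On the standardized scale, extra starters 0.5 or 1.0 SD lower shift the difference by 0.08 or 0.17 SD, which is 17% or 33% of the planned 0.5.

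**4. Sensitivity to the one-sixth.** In general the shift is (extra share) × (a − A). For gaps of −20 to −50 points, an extra share of 10% gives −2 to −5 points and a share of 25% gives −5 to −12.5.

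**5. Against sampling error.** With 67 and 80.4 starters at 70%, the standard error of the difference is √[0.70×0.30×(1/67+1/80.4)] = 7.6 points. The illustrated shifts are at most about one standard error.

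**6. Change between visits.** If adherence were 80% under JomPrEP and 70% under TAU at months 3, 6 and 9, the percent change would be 0 in both arms, although the level differs by 10 points throughout.

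**The case against.** The strongest reply is that the direction of the bias is unknown. A reader might infer that JomPrEP will look worse the more reluctant men it brings in. The documents do not support that as a prediction. The Introduction reports low uptake despite strong interest and names fear of disclosure, stigma, waits and repeated visits as barriers, and Expected Findings says that the app removes such barriers. The extra starters may therefore be motivated men who lacked access, and may adhere as well or better. The Introduction also lists mental illness and low perceived risk, so neither direction can be assumed. This stands, and the point is limited to bias of unknown sign.

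Other replies also carry weight:

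- **Uptake is not initiation.** Primary Outcomes defines uptake as current use. Men who start and stop are then missed, and the proportion ever starting is not given. The one-sixth is an assumption.
- **Part of the remedy exists.** Current PrEP use at month 9 in all randomized men is already a primary outcome, so no additional on-PrEP measure is needed for persistence.
- **The change contrast is only an alternative.** The main adherence analysis follows the primary one, which compares month-9 levels, and the linear mixed model still contains a treatment term.
- **Start times.** A reader might infer that the arms are compared at different times since initiation. No section gives start times by arm, and the time origin of the Cox model is ordinary analysis-plan detail.
- **Size.** A shift of at most about one standard error can mask a benefit but is unlikely on its own to produce a firm reversed conclusion.

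None of this answers the core: the restriction is fixed in the outcome definition, the table and the analysis, and no randomized version of adherence is offered beside it.

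**Conclusion.** The point holds for the secondary outcomes. As written, the plan compares arms on adherence and persistence within a group defined after randomization by a behavior the intervention targets, and treats the difference as a treatment effect. The bias can go either way. If 50% v 60% is initiation and JomPrEP deters nobody, it equals one sixth of the adherence gap between the extra starters and the others: -8 to -3 points for an assumed 20-50% v 70%, zero for no gap, and in JomPrEP's favor for a positive gap. The primary comparisons are untouched, because they include all randomized participants. The plan should be changed, but the trial's main conclusion does not depend on it.

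**What to change.** 1. Define the secondary adherence comparison in all randomized participants: on PrEP with tenofovir-diphosphate at or above the plan's own 700 fmol/punch threshold at month 9. Count confirmed non-starters as no, and handle participants of unknown status under Plan for Missing Data.
2. Keep starter-only adherence and persistence, including the Cox analysis, but label them non-randomized and descriptive. Read persistence beside the existing all-randomized primary outcome of current PrEP use.
3. In the alternative continuous analysis, contrast the month-9 level and not only changes between follow-up visits.

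Cost: no new blood spots are needed from non-starters, because uptake is already recorded for everyone at each visit with record review for confirmation. More than analysis wording changes, though. The definition in Secondary Outcomes and the Table 1 footnote must be amended, and the 85% power statement must be relabelled as applying to the starter-only analysis. The new measure combines starting with adhering, so it does not isolate adherence. Its power may be low: for the illustrative 35.0% v 40.5% at 121 per arm it is about 22% one-sided and 14% two-sided. It should therefore be reported as an estimate with its interval.

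### The month-9 uptake proportions are to come from a random-subject mixed-model contrast, which under a logit link does not estimate the arm proportions named in the hypothesis

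*Protocol article*

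**What the plan says.** Three statements in the protocol article bear on this.

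- **Target.** The Analytical Plan says "we will compare the proportion for both outcomes" and defines the two quantities in the null hypothesis, p_I and p_TAU, by saying that they "are the proportion of HIV testing and PrEP uptake in the JomPrEP and TAU groups, respectively". These are proportions of each randomised arm.
- **Planning values.** The Sample Size section works on the same scale. It sizes the trial on a gain of 10 percentage points, "assuming 50% PrEP uptake in the TAU group at the 1-sided .05 significance level", and later takes 60% for the JomPrEP group.
- **Estimator.** For the primary binary outcomes the Analytical Plan says that "a generalized linear mixed model [50] with random subject effects will be built to account for the correlation in repeated measurements within participants". The month-9 quantities then follow: "HIV testing and PrEP uptake proportion at the 9-month follow-up will be estimated and compared using a linear contrast statement in SAS PROC GLIMMIX".

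The article gives no link function, fitting method, random-effect variance or within-person correlation for these outcomes. It describes no step that turns the contrast into an arm proportion.

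**The concern.** A linear contrast acts on the linear predictor. In a mixed model with a random subject effect and a logit link, a treatment contrast at month 9 is a subject-specific log odds ratio, and the inverse link of an arm's linear predictor is the probability for a participant with random effect zero. The proportion of the arm is the average of the inverse link over all participants. Because the inverse logit is curved, the two differ unless the random-effect variance is zero or the proportion is exactly one half.

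So the plan names one quantity as its target and another as its estimate of that target. The month-9 figures would be read as uptake in each arm. They could disagree with the raw proportions in the same report, and the effect size could look larger than the difference on which the trial was planned. The gap grows with within-person correlation. That correlation may be substantial when current PrEP use is recorded on the same person at 3, 6 and 9 months, but the article gives no value.

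**Working it through.** **Inputs.** From the Sample Size section: 50% in TAU and 60% in JomPrEP. From Primary Outcomes: three visits. Assumed, because the article is silent: a logit link, a normal random intercept with the same SD σ in both arms, and a range for σ.

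**The plan's own scale.** The planned effect is 60% − 50% = 10 percentage points. As an odds ratio of arm proportions it is (0.60/0.40) / (0.50/0.50) = 1.50. The article gives no model-based month-9 figure to reproduce.

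**Step 1: arm proportion and model value.** For an arm with linear predictor η, the arm proportion is

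p = ∫ expit(η + σb) φ(b) db, with b standard normal.

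The back-transformed contrast value is expit(η). I solved the integral numerically for the η that gives p = 0.60, then evaluated expit(η). For p = 0.50 symmetry gives η = 0 and expit(0) = 0.50 whatever σ is. The odds ratio below is therefore expit(η)/(1 − expit(η)) for JomPrEP, since the TAU odds are 1.

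| Assumed SD σ | Visit-to-visit correlation (at 50%) | JomPrEP value at random effect zero | TAU | Odds ratio |
|---|---|---|---|---|
| 0 | 0 | 60.0% | 50% | 1.50 |
| 0.5 | 0.06 | 60.6% | 50% | 1.54 |
| 1 | 0.17 | 62.0% | 50% | 1.63 |
| 1.5 | 0.29 | 63.9% | 50% | 1.77 |
| 2 | 0.39 | 66.1% | 50% | 1.95 |
| 3 | 0.54 | 70.7% | 50% | 2.41 |
| 4 | 0.64 | 75.2% | 50% | 3.03 |

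Worked line: at σ = 2 the solution is η = 0.668, expit(0.668) = 0.661, and 0.661/0.339 = 1.95. Putting η = 0.668 and σ = 2 back into the integral returns 0.600.

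TAU is unmoved only because 50% is the symmetric point. As an illustration with rates that are not in the article, 20% v 30% at σ = 3 would appear as 5% v 14%.

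**Step 2: dependence on the fitting method.** The table shows what the model's true parameters imply. What software prints also depends on how the model is fitted. Data were simulated with 8,000 per arm, three visits, a logit random intercept, and true arm proportions of 50% and 60% at every visit. The same data were fitted by maximum likelihood with quadrature and by residual pseudo-likelihood. Month-9 values, TAU / JomPrEP:

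| SD σ | Raw | Quadrature | Pseudo-likelihood |
|---|---|---|---|
| 1 | 49.6 / 60.1% | 49.5 / 62.2% | 49.6 / 60.5% |
| 2 | 50.3 / 60.1% | 50.4 / 66.7% | 50.3 / 61.6% |
| 3 | 50.3 / 59.6% | 50.6 / 69.9% | 50.3 / 61.8% |
| 4 | 50.6 / 59.9% | 51.7 / 74.9% | 50.8 / 63.0% |

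Pseudo-likelihood estimated the random-effect variance far too low (3.15 against a true 16 at σ = 4), so its values stay near the raw ones. At σ = 4 the two methods report about 63% and 75% for an arm with 60% uptake.

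**Step 3: the test.** For a fixed σ the integral in Step 1 is strictly increasing in η. If both arms share σ, p_I = p_TAU holds exactly when the two η are equal. A test of the contrast is then a test of the stated null hypothesis.

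**Step 4: after correction.** Averaging expit(η + σb) over b returns 60% and 50% at every σ. A marginal model targets the same two values directly.

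**The case against.** Four points can be made for the plan.

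1. **The article is condensed.** Link, fitting method and back-transformation are details that may sit in a full protocol or SAP. This stands in part: their absence alone is no fault. But the article does fix the target, the class of model and the statement that is to produce the proportions, and these do not agree as written.
2. **The hypothesis test is sound.** This stands, under a common random-effect variance. The point concerns estimation only.
3. **The subject-specific odds ratio is a legitimate quantity.** True, and a random-intercept model is a standard analysis of repeated binary data. But the article calls the result an uptake proportion and states its hypothesis in arm proportions, so the difference is more than one of taste.
4. **The distortion may be small.** This stands. With an SD of 1.5 or less it is at most about 4 points, and under pseudo-likelihood it was about 3 points or less even at an SD of 4. That is not a safeguard, though, because the headline figure would then turn on a fitting choice that the article does not state.

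A reader might infer that the trial will report 66-75% for a true 60%. The documents do not support that. The range needs a logit link, an SD of about 2-4, quadrature fitting, and reporting of the inverse link at random effect zero. The article states none of these.

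**Conclusion.** The target and the estimator do not match. The hypothesis is about arm proportions, and the named random-subject contrast, under a logit link, yields a value conditional on the subject effect. The primary test is not undermined if the random-effect variance is common to the arms. The reported month-9 proportions and effect size can be.

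The size can only be given as a range, because it rests on assumptions outside the article. For a true 60% v 50% it is about 61-64% v 50% at SDs of 0.5-1.5 and 66-75% v 50% at SDs of 2-4 under quadrature, and about 60.5-63% v 50-51% at SDs of 1-4 under pseudo-likelihood. The plan should be corrected on this point, but it does not threaten the efficacy decision. Whether the planned number of participants is adequate is a separate question that neither supports nor weakens this one.

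**What to change.** Define the month-9 estimate for each primary outcome as the difference between arms in marginal (population) proportions, with a confidence interval. Either of two routes will do:

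- fit the mixed model by adaptive quadrature and average its predictions over the random-effect distribution and the covariates; or
- use GEE or logistic regression, with standardisation over covariates.

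The mixed-model test may be kept. Its inverse-link contrast should not be reported as the arm's uptake proportion. If the subject-specific odds ratio is reported, label it as such and state the link and fitting method.

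The cost is a sentence or two of analysis text and a few lines of code, with no extra data or participants. The effect will usually look less favourable than the conditional odds ratio, but it will be on the scale of the hypothesis and the planning assumptions.

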#### Phase IIA: Efficacy Trial of JomPrEP

##### Study Design

We will conduct a prospective randomized controlled trial to evaluate the efficacy of JomPrEP versus treatment as usual (TAU) among MSM in Malaysia for primary (ie, HIV testing and PrEP uptake) and secondary (ie, PrEP adherence and persistence) outcomes over 9 months of observation. We will enroll 268 participants who will be randomized (1:1) to receive either JomPrEP or TAU and will be followed for 9 months (assessments at 3, 6, and 9 months; Figure 1).

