## Discussion

### Expected Findings

In this study, we propose to develop and test the efficacy of a clinic-integrated app (ie, “JomPrEP”). JomPrEP will be designed to virtually deliver an integrated HIV prevention intervention that will promote HIV testing and linkage to PrEP. We hypothesize that JomPrEP will be significantly more effective in improving uptake of HIV testing and PrEP among MSM in Malaysia. We also anticipate that the results and qualitative feedback from participants and stakeholders will inform the refinement of JomPrEP for a future implementation trial.

JomPrEP will help to reduce some of the individual- (eg, lack of information, psychiatric and substance use disorder, negative experiences with clinicians, low perceived risk) and structural-level barriers (eg, long waits and multiple visits, stigma, and discrimination from physicians) to HIV testing and PrEP care in multiple ways, by (1) offering relevant information and resources on PrEP, HIV risk reduction, and psychiatric and substance use disorder support services; (2) incorporating on-demand features with real-time e-Counseling, tracking, and monitoring linked and integrated with clinical services within 1 platform to deliver seamless transition without any in-person interaction with the clinicians. This enhancement on the traditional O2O service delivery model ensures open and nonjudgmental virtual space for MSM to discuss various issues with the clinicians without fear of stigma and discrimination [30,31]; (3) decreasing long clinic wait times and reducing the number of clinical visits; and (4) collaborating with local clinics and other stakeholders to deliver seamless, integrated HIV prevention services care as well as to ensure sustainability and further expansion of JomPrEP. If successful, JomPrEP will be among the first clinic-integrated apps to deliver comprehensive HIV prevention services for MSM in LMICs, including Malaysia. Furthermore, the app could be an innovative platform to link online service utilization and subsequent offline clinical services uptake (eg, HIV treatment services, psychiatric care).

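### Binary PrEP persistence and adherence are modelled by study visit, so if JomPrEP users start PrEP sooner the arms are compared at unequal time on PrEP

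*Protocol article*

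**What the plan says.** All locations are in the protocol article.

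- **Clock.** Under Study Design, participants are followed for 9 months from randomization, with assessments at 3, 6 and 9 months. Under Study Settings and Participants, current PrEP users are excluded, so every start falls after enrolment. Under Primary Outcomes, uptake is read at each of the three visits, and no latest start is given.
- **Adherence.** Secondary Outcomes plans "dried blood spot testing at 3-, 6-, and 9-month follow-ups", with a binary threshold for optimal adherence. Table 1 puts the Visual Analog Scale at the same visits, for PrEP starters only.
- **Persistence.** Secondary Outcomes says: "Persistence on PrEP will be measured based on the completion of quarterly PrEP visits". Table 1 again limits this to starters, at study months 3, 6 and 9.
- **Analysis.** The Analytical Plan specifies a generalized linear mixed model with treatment, time and their interaction, and a contrast at month 9 for the primary outcomes. It continues: "Similar analyses will be conducted for the secondary binary outcomes: optimal adherence and PrEP persistence". Time since PrEP start is not named as a term.
- **A second persistence analysis.** The same section plans time to discontinuation with a Cox model among those starting PrEP. It does not state the time origin.
- **Mechanism.** Expected Findings says that JomPrEP will work partly by "decreasing long clinic wait times and reducing the number of clinical visits".

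**The concern.** Adherence and persistence describe what happens after a man starts PrEP, so their natural clock begins at that start. The binary model runs on time since randomization. The two clocks differ by each man's delay to starting, and shortening that delay is one of the things JomPrEP is designed to do.

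If it succeeds, JomPrEP starters will on average have been on PrEP longer at month 9 and will have had more time to stop. A difference in persistence can then appear with no difference in stopping behaviour, and it runs against the intervention. A true benefit could be hidden, or a false harm reported. This is separate from the question of who chooses to start: it would arise even if the same kind of men started in both arms.

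Visit-based persistence has a further gap. A man who starts after month 6 has less than a quarter on PrEP when follow-up ends, and the article does not say how he is scored.

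**Working it through.** **1. The plan's own figure.** Sample Size gives 85% power for a standardized effect of 0.5 on adherence and persistence. Take 134 per group (268/2), with uptake of 60% in JomPrEP and 50% in TAU: 80.4 and 67 starters. The standard error is √(1/80.4 + 1/67) = 0.1654, and 0.5/0.1654 = 3.02. Two-sided 0.05 power is Φ(3.02 − 1.96) = 85.6%, which reproduces the figure. At one-sided 0.05 the same inputs give 91.6%.

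**2. Size of the artefact, single start time per arm.** Inputs are assumed: the same monthly stopping rate r in both arms, and all men in an arm starting at the same month s. The proportion still on PrEP at month 9 is (1 − r)^(9 − s).

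| Monthly stopping | Start, JomPrEP v TAU | JomPrEP | TAU | False deficit |
|---|---|---|---|---|
| 5% | month 1 v 4 | 0.95^8 = 66.3% | 0.95^5 = 77.4% | 11.0 points |
| 2% | month 1 v 4 | 0.98^8 = 85.1% | 0.98^5 = 90.4% | 5.3 points |
| 5% | month 1 v 2 | 0.95^8 = 66.3% | 0.95^7 = 69.8% | 3.5 points |

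**3. Spread start times.** Starts were simulated as uniform within a window, with exponential stopping at the same hazard in both arms, and 80 v 67 starters. The test is two-sided at 0.05.

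- JomPrEP starts in months 0–3 and TAU starts in months 0–9 (mean time on PrEP at month 9: 7.5 v 4.5 months). If 90% of men remain on PrEP 3 months after starting, month-9 persistence is 76.8% v 85.7%. At 80% it is 57.4% v 73.0%, and at 70% it is 41.1% v 61.4%. The false deficit is 9 to 20 points, and the test rejects 28% to 70% of the time.
- JomPrEP starts in months 0–6 and TAU starts in months 0–9: the false deficit is about 4.5 to 11 points, with 12% to 28% rejection.
- Same start window in both arms: no deficit, 5% rejection.

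In every scenario, retention measured 3 months after each man's own start is equal between arms. The artefact therefore comes only from the clock.

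**4. Late starters.** If starts were spread evenly over 9 months, (9 − 6)/9 = one third would start after month 6 and could not show a full quarter on PrEP.

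**5. Cost of restricting to men with at least 3 months on PrEP.** Keep 67% of starters in each arm: 53.9 v 44.9 men. The standard error is √(1/53.9 + 1/44.9) = 0.202, and 0.5/0.202 = 2.47. Two-sided power is Φ(2.47 − 1.96) = 69.6%, against 85.6% in step 1. If one third are lost in TAU only, power is 76.5%. If 10% are lost in JomPrEP and 50% in TAU, it is 66.7%.

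**The case against.** The strongest reply is that the plan already contains much of the remedy. Time to discontinuation among starters would naturally run from PrEP start and censor late starters at month 9, and a Cox analysis run that way is free of the artefact above. This stands in part: persistence is not read only at months since randomization. But the origin is unstated, the binary analysis sits beside the Cox analysis with no order between them, and adherence has no time-to-event analysis to fall back on.

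It can also be said that similar does not mean identical, that the month-9 contrast is stated only for the primary outcomes, and that the model admits further hypothesized confounders. An analysis plan that is not shown could use that room. Still, the model that the article states is by study visit, and nothing in it points to time on PrEP.

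Three stronger readings are tempting and are not supported:

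- A reader might infer that late starters cannot be assessed at all. They can: anyone who starts before month 9 can give a month-9 blood spot and Visual Analog Scale, and contributes censored time to a Cox model. The limit concerns only a completed quarter of visits after a start later than month 6.
- A reader might infer that such men will be scored as non-persistent, or as trivially persistent. The article gives no rule, and treating them as not applicable or censored is equally open.
- A reader might infer that recent starters will fall below the blood-spot threshold despite full dosing. The article says the drug is measured in red cells but not how fast it accumulates, so neither the direction nor the size of a bias in adherence can be claimed from it.

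**Conclusion.** The point holds for the stated binary analysis. Read as written, it compares starters at equal time since randomization, not at equal time on PrEP. If JomPrEP brings starts forward, the persistence contrast is biased against JomPrEP: by 3.5 to 11 points in the single-start illustrations, and by about 4.5 to 20 points with spread starts and a wider range of stopping rates. If start times are alike in the two arms, the bias is zero. All these sizes rest on assumed start times and stopping rates, because the article gives neither; only the direction for persistence follows from its stated aim of faster access.

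For adherence, the supportable conclusion is weaker: time on PrEP may differ by arm at each sample and is not accounted for. For the Cox analysis, the defect is an unstated origin and no stated priority. Both outcomes are secondary, so the primary comparison is untouched. The change is worth making because it is cheap and the stated binary analysis can produce a false difference.

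**What to change.** 1. Record the PrEP start date in both arms. The self-report and medical record review already planned to confirm uptake can supply it.
2. Name the Cox analysis as the lead persistence analysis, with time zero at PrEP start and censoring at month 9.
3. Make any binary persistence comparison at a common time since start (for example 3 months), only among men whose quarterly visit has fallen due, and label it supportive.
4. Add time since PrEP start to the adherence model. Add a sensitivity analysis limited to samples taken after a prespecified minimum time on PrEP, the same in both arms.

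The cost is one date field and a few lines of text. The restricted binary analyses do lose late starters: if one third start after month 6, power for a 0.5 SD effect falls from about 86% to about 70%. That is why they should be supportive, while the censored analysis, which keeps late starters, leads. These changes align the clocks. They do not remove the separate limitation that men who start PrEP in each arm are a self-selected subset of those randomized.
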